### Objectives

2.6

#### Primary

2.6.1

To describe the incidence of postoperative diaphragmatic dysfunction (PDD) and explore its association with postoperative pulmonary complications (PPCs) after minimally invasive thoracic surgery (VATS and RATS).

#### Secondary

2.6.2

To identify potential risk factors (such as surgical technique) of PPCs and to evaluate the clinical application of diaphragm ultrasound examination.

### Endpoints

2.7

#### Primary endpoint

2.7.1

Incidence of PDD (DE values less than 10 mm or negative) at 1 day postoperatively.

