#### Secondary endpoints

2.7.2

(1) Incidence and severity of PPCs at 7 days postoperatively; (2) T0-T3 diaphragm function at different time points (DTF, DE and the difference of DE between T1/2/3 and T0). (3) NRS scores and Ramsay sedation scores at different time points. (4) QoR-15 scores at different time points.

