### Sample size calculation

2.8

Sample size is recalculated based on the primary predictive objective (logistic regression for the association between PDD and PPCs). Based on the literature review of perioperative PPCs incidence in minimally invasive thoracic surgery (VATS/RATS) with standardized EPCO complication definitions and complete 7-day postoperative follow-up and our pilot study, the baseline PPC incidence of 37% was selected as the core assumption for this power analysis and sample size calculation; Assuming a PDD incidence of 30% postoperatively (7, 12), a PPCs incidence of 37% in the study population (1–5, 15, 32), an odds ratio (OR) of 3.0 for PDD predicting PPCs (7, 28), alpha = 0.05, power = 0.80, and 10% dropout rate, a minimum of 148 patients in total is required. Sample size estimation is performed using PASS software (PASS 15 Power Analysis and Sample Size Software (2017). NCSS, LLC. Kaysville, Utah, United States)^1^ with logistic regression parameters accounting for covariates (age, BMI, ASA classification), and the above parameter selection fully aligns with the literature review results of PPCs incidence in minimally invasive thoracic surgery, ensuring the consistency between clinical evidence and statistical methodology.

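### The sample size and its 80% power belong to the PDD–PPC odds ratio, which the endpoint list does not make primary, and 148 shows no visible allowance for the named covariates

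*Protocol article*

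**What the plan says.** Four places in the protocol article bear on this.

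- **Primary objective (2.6.1):** "To describe the incidence of postoperative diaphragmatic dysfunction (PDD) and explore its association with postoperative pulmonary complications (PPCs" and so on. It has two parts, one descriptive and one exploratory.
- **Primary endpoint (2.7.1, repeated in the abstract):** "Incidence of PDD (DE values less than 10 mm or negative) at 1 day postoperatively". No null value, hypothesis or interval width goes with it.
- **Secondary endpoints (2.7.2):** the first item is "Incidence and severity of PPCs at 7 days postoperatively".
- **Sample size (2.8):** "Sample size is recalculated based on the primary predictive objective (logistic regression for the association between PDD and PPCs"). The inputs are "Assuming a PDD incidence of 30% postoperatively", "a PPCs incidence of 37% in the study population" and "an odds ratio (OR) of 3.0 for PDD predicting PPCs", with alpha 0.05, power 0.80 and 10% dropout, giving at least 148 patients. The calculation is described as run "with logistic regression parameters accounting for covariates (age, BMI, ASA classification"). It gives no R² of PDD on those covariates and no sidedness for alpha.

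The statistical analysis section (2.9) handles PPC by forward stepwise logistic regression to look for risk factors. It does not single out one prespecified PDD–PPC model.

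**The concern.** The only power statement in the article concerns a model whose outcome is a secondary endpoint. In that calculation the primary quantity, PDD incidence, appears only as the prevalence of the predictor. The association is called a primary predictive objective in 2.8, something to explore in 2.6.1, and by its outcome secondary in 2.7.2.

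What is at stake is which result counts as confirmatory. As written, the 80% power could be read across to a percentage that is not tested. Alternatively, a formally secondary association could become the headline once the data are known.

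There is a related doubt within 2.8. If the calculation allowed for covariates, the total should exceed that of the corresponding unadjusted calculation, and it is not clear that it does.

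**Working it through.** **Inputs (all from 2.8).** PDD prevalence B = 0.30; overall PPC risk 0.37; OR = 3.0; alpha 0.05, taken here as two-sided; power 0.80; dropout 10%.

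**Step 1. PPC risks by PDD status.** Solve 0.7·p0 + 0.3·p1 = 0.37 with odds(p1) = 3·odds(p0). Result: p0 = 0.2917 without PDD and p1 = 0.5527 with PDD.

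**Step 2. Reproduce 148 (Wald test of the log odds ratio, no covariates).**

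- V = 1/(0.7·p0·q0) + 1/(0.3·p1·q1) = 6.914 + 13.483 = 20.397
- N = (1.960 + 0.8416)² · V / (ln 3)² = 7.849 · 20.397 / 1.2069 = 132.6, so 133 evaluable
- 133 / 0.9 = 147.8, so **148**

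This matches the stated figure with no covariate inflation.

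**Step 3. Sensitivity to the formula.**

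| Variant (two-sided) | Evaluable | With 10% dropout |
|---|---|---|
| Wald, 37% as overall PPC risk | 133 | 148 |
| Wald, 37% as risk without PDD | 134 | 149 |
| Hsieh, binary predictor, 37% overall | 129 | 144 |

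Hsieh before rounding is 128.2, so 133 evaluable would leave room for R² = 1 − 128.2/133 = 0.036.

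**Step 4. What an allowance would have cost.** Covariate adjustment divides N by (1 − R²). With the Wald formula and dropout:

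- R² 0.05: 133/0.95 = 140; 140/0.9 gives 156
- R² 0.10: 133/0.90 = 147.8, so 148; 148/0.9 gives 165

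**Step 5. Power at 133 evaluable.** Wald power = Φ(ln 3 · √(133(1 − R²)/20.397) − 1.96). R² is assumed, since the article states none.

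| R² | ln 3 · √(·) | Wald power | Hsieh power |
|---|---|---|---|
| 0 | 2.805 | 0.80 | 0.81 |
| 0.10 | 2.661 | 0.76 | 0.77 |
| 0.20 | 2.509 | 0.71 | 0.72 |

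**Step 6. One-sided alpha.** The same Wald formula gives 104.5 evaluable. Then 133 would absorb R² = 1 − 104.5/133 = 0.21, and power at R² 0.20 would be 0.81.

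**Step 7. Precision of the named primary endpoint.** At 30% PDD the 95% half-width is 1.96·√(0.3·0.7/133) = 0.078 with 133 evaluable, and 1.96·√(0.3·0.7/148) = 0.074 with all 148. The article gives neither figure.

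**The case against.** The strongest reply is that the association already sits in the second half of the primary objective, that the title and stated aim point the same way, and that 2.8 says openly what it sizes. This stands as far as it goes: the sample size does match part of the primary objective. It does not settle the hierarchy, because the objective only explores the association and the endpoint list makes its outcome secondary.

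A reader might infer that the article claims 80% power for PDD incidence. It does not; no sentence says so. A descriptive proportion also needs no test or power, and ±7.8 points is usable precision. What is missing is a statement of that precision, and of where the power belongs.

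A reader might also infer that the authors made no covariate allowance and that the power is therefore overstated. The documents do not prove this. The exact match is to one formula with two-sided alpha; the Hsieh formula leaves room for R² of about 0.04, and a one-sided alpha for about 0.21. The article says that covariates were accounted for. The fair statement is that the allowance cannot be seen in the number and that the inputs needed to check it are not given.

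Finally, one might want the odds ratio to replace the primary endpoint. Section 2.1 dates the operations July 2025 to May 2026 and the article appeared in March 2026, so that would be a late change of primary endpoint. It is not needed to cure the fault.

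**Conclusion.** The point holds as a mismatch between primary objective, primary endpoint and sample size. The 80% power is for detecting an odds ratio of 3.0 for PPC, which the endpoint list does not make primary. The primary endpoint, day-1 PDD incidence, has no stated precision.

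The covariate statement is a second, conditional part. The total of 148 equals the unadjusted two-sided Wald figure. If alpha is two-sided, adjusted Wald power at 133 evaluable is about 0.76 at R² 0.10 and 0.71 at R² 0.20, against the stated 0.80. This rests on assumed R² values and on 2.8's own rates and odds ratio.

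None of this shows that 148 is an arithmetic error or that the study is too small. The sum reproduces, and the precision for PDD incidence is adequate for description.

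**What to change.** 1. **2.7.1 and abstract:** keep day-1 PDD incidence as the primary endpoint and add its expected precision: 95% CI about ±7.8 points at 30% PDD with 133 evaluable patients.
2. **2.7.2 and 2.9:** name the odds ratio of any 7-day PPC for day-1 PDD, adjusted for the prespecified age, BMI and ASA class, as the single powered key secondary analysis. This matches the second half of the primary objective. Keep it separate from the stepwise risk-factor search. The expected 0.37 · 133 = 49 events support four variables under the article's own rule of ten events per variable, if ASA class is entered as one term.
3. **2.8:** say that the 0.80 power refers to that odds ratio and not to the primary endpoint. Then either give the R² and the sidedness used, or restate 0.80 as the unadjusted power and add the adjusted range (about 0.76 at R² 0.10 and 0.71 at R² 0.20, two-sided).

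The cost is wording changes and possibly a slightly less favourable stated power. No extra patients are needed and the primary endpoint does not change.

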#### Secondary endpoints

2.7.2

(1) Incidence and severity of PPCs at 7 days postoperatively; (2) T0-T3 diaphragm function at different time points (DTF, DE and the difference of DE between T1/2/3 and T0). (3) NRS scores and Ramsay sedation scores at different time points. (4) QoR-15 scores at different time points.

### Sample size calculation

2.8

Sample size is recalculated based on the primary predictive objective (logistic regression for the association between PDD and PPCs). Based on the literature review of perioperative PPCs incidence in minimally invasive thoracic surgery (VATS/RATS) with standardized EPCO complication definitions and complete 7-day postoperative follow-up and our pilot study, the baseline PPC incidence of 37% was selected as the core assumption for this power analysis and sample size calculation; Assuming a PDD incidence of 30% postoperatively (7, 12), a PPCs incidence of 37% in the study population (1–5, 15, 32), an odds ratio (OR) of 3.0 for PDD predicting PPCs (7, 28), alpha = 0.05, power = 0.80, and 10% dropout rate, a minimum of 148 patients in total is required. Sample size estimation is performed using PASS software (PASS 15 Power Analysis and Sample Size Software (2017). NCSS, LLC. Kaysville, Utah, United States)^1^ with logistic regression parameters accounting for covariates (age, BMI, ASA classification), and the above parameter selection fully aligns with the literature review results of PPCs incidence in minimally invasive thoracic surgery, ensuring the consistency between clinical evidence and statistical methodology.

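### The 148 patients are said to allow for covariates, but the listed inputs give 148 with no such allowance and leave room for at most a very small one (two-sided test assumed)

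*Protocol article*

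**What the plan says.** Section 2.8 (Sample size calculation) sizes the study on a logistic regression of PPCs on PDD. The inputs are:

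- "Assuming a PDD incidence of 30% postoperatively"
- "a PPCs incidence of 37% in the study population"; the same section also says that "the baseline PPC incidence of 37% was selected as the core assumption"
- "an odds ratio (OR) of 3.0 for PDD predicting PPCs"
- "alpha = 0.05, power = 0.80, and 10% dropout rate, a minimum of 148 patients in total is required"

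The section then says that the software was run "with logistic regression parameters accounting for covariates (age, BMI, ASA classification"). It gives no R-squared of PDD on those covariates and no other covariate allowance. It does not say whether alpha is one-sided or two-sided, and it names the software but not the formula.

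The Abstract promises multivariate regression to adjust for confounders. Section 2.9 plans a forward stepwise logistic model for risk factors of PPCs.

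**The concern.** In a logistic model, correlation between the exposure and the other covariates inflates the variance of the exposure coefficient by about 1/(1 − R²), where R² is the share of the variance of PDD explained by the covariates. A calculation that really allows for age, BMI and ASA should therefore give a larger number than one that ignores them. If the listed inputs reach 148 without any allowance, the 80% power describes the crude PDD–PPC odds ratio. A reader of section 2.8 would nevertheless take it to hold for the adjusted odds ratio, which is the one of interest when PDD is put forward as a risk factor beyond patient characteristics.

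**Working it through.** **Inputs (section 2.8).** Share with PDD R = 0.30; PPC incidence 0.37; OR = 3.0; alpha 0.05, assumed two-sided (z = 1.960); power 0.80 (z = 0.842); dropout 10%. (1.960 + 0.842)² = 7.849 and (ln 3)² = 1.207.

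**1. Reproducing 148 with no covariate allowance, 37% read as the overall rate.**

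Solve 0.7·P0 + 0.3·P1 = 0.37 with OR 3: P0 = 0.2917 without PDD, P1 = 0.5527 with PDD.

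Wald formula:

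- V = 1/(0.7·P0·Q0) + 1/(0.3·P1·Q1) = 1/0.1446 + 1/0.0742 = 20.40
- N = 7.849 × 20.40 / 1.207 = 132.6, so 133 evaluable
- 133/0.9 = 147.8, so **148 enrolled**

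Log-odds-ratio score formula:

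- N = 7.849 / (0.37 × 0.63 × 0.30 × 0.70 × 1.207) = 132.85, so 133 evaluable and again **148 enrolled**

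A simulation of the unadjusted model at n = 133 gave power 0.806.

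**2. Other readings, still with R² = 0.**

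| Formula | 37% read as | Evaluable | Enrolled | R² that brings it to 133 evaluable |
|---|---|---|---|---|
| Wald | overall rate | 132.6 → 133 | 148 | none |
| Wald | rate without PDD (P1 = 0.638) | 133.7 → 134 | 149 | none |
| Difference of proportions | overall rate | 128.2 → 129 | 144 | about 0.036 (0.03 gives 132.2 → 133) |
| Difference of proportions | rate without PDD | 126.4 → 127 | 142 | about 0.05 (gives 133.0) |

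The difference-of-proportions form is N = {1.960·√[P·Q/R] + 0.842·√[P0·Q0 + P1·Q1·(1 − R)/R]}² / [(P0 − P1)²·(1 − R)], where P is the overall rate and Q = 1 − P. So among the two-sided readings tried, 148 contains an allowance of between zero and about 0.05.

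**3. What adjustment would cost.** The article gives no R², so the values below are assumptions. Wald formula, 37% overall. Power at 133 evaluable is Φ(ln 3/SE − 1.960), with SE = √[20.40/(133·(1 − R²))]. The N needed is 132.6/(1 − R²), rounded up, then divided by 0.9.

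| R² | SE | Power at OR 3.0 | OR detectable with 80% power | Enrolled for 80% power at OR 3.0 |
|---|---|---|---|---|
| 0 | 0.392 | 80% | 3.0 | 148 |
| 0.05 | 0.402 | 78% | 3.1 | 156 |
| 0.10 | 0.413 | 76% | 3.2 | 165 |
| 0.20 | 0.438 | 71% | 3.4 | 185 |

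**The case against.** A reader might infer from the match that 148 was certainly computed with no allowance, and that 80% power and the covariate claim cannot both be true. The documents do not support that. The match depends on the formula and on how 37% is read, and section 2.8 calls that figure both the baseline incidence and the incidence in the study population. Under the difference-of-proportions formula, 148, 80% power and a small covariate allowance are compatible. Sidedness is also unstated. A one-sided 5% test would need only about 99 to 105 evaluable, and 133 would then contain an R² of about 0.21 to 0.25. Nothing in the article indicates a one-sided test, but nothing rules it out.

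Three further points have weight.

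- An R² entered in software is a detail that a condensed article may leave out. That stands as far as the omission goes. But the article makes a positive claim about how 148 was obtained, and the inputs it lists reach that number without the claimed element.
- The plan fixes no PPC model with exactly age, BMI and ASA. Section 2.9 names those three only among the propensity-score variables for VATS against RATS, and the PPC model is chosen stepwise. That stands, so any restatement should refer to a covariate-adjusted model in general.
- The loss may be small. Eligibility in section 2.2 restricts age, BMI and ASA class and excludes preoperative diaphragm insufficiency, so a low R² is plausible. The primary objective only explores the association, and the primary endpoint is PDD incidence. This limits the consequence but does not make the sentence in section 2.8 accurate.

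**Conclusion.** The concern holds in limited form. With a two-sided test, the listed inputs support 80% power for an unadjusted odds ratio of 3.0. They support it for an adjusted one only if the covariates explain almost none of PDD: an R² of at most about 0.05 under the most favourable formula, and zero under Wald. That the allowance was in fact zero is not established.

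The shortfall is negligible to moderate. Power is about 78% at R² 0.05 and about 71% at 0.20. Those figures rest on the assumed R², a two-sided alpha, 37% as the overall rate and the Wald formula. The difference-of-proportions formula gives slightly higher power at R² 0.10 and 0.20 (about 77–78% and 72–73%).

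**What to change.** Keep 148 and reword the paragraph in section 2.8 along these lines:

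> With 10% dropout, 148 enrolled patients leave 133 evaluable and give 80% power (two-sided alpha 0.05) for an unadjusted PDD–PPC odds ratio of 3.0. In a covariate-adjusted model, power would be about 78%, 76% or 71% if the covariates explain 5%, 10% or 20% of the variance of PDD (assumed values). The odds ratio detectable with 80% power would then be about 3.1, 3.2 or 3.4.

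In addition, either state the R² and the sidedness entered in the software, or delete the statement that the calculation accounts for covariates. If the software run turns out to have used a one-sided alpha, the figures above must be recomputed on that basis.

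The cost is one reworded paragraph and a slightly less favourable stated power. No more patients and no change to the analysis are needed.

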### Statistical analysis

2.9

Percentages will be calculated for dichotomous data and analyzed by the Pearson chi-square test or Fisher exact test. Continuous variables will be expressed as mean standard deviation (Mean ± SD) and median (ranging from 25th to 75th percentiles), and Student’s *t*-test was used for comparison between groups; The paired sample *t*-test is used for comparison of the same index. Propensity Score Matching (PSM) will be performed to balance baseline characteristics (e.g., age, BMI, ASA classification, tumor complexity) between the VATS and RATS groups (1:1 matching ratio, caliper width 0.2 SD) to mitigate selection bias. A baseline characteristics table will be added as Table 1 in the final manuscript, which will present the demographic, clinical and surgical-related baseline data of the VATS and RATS groups before and after PSM matching, so as to clearly show the balance effect of the matching process on the baseline characteristics between the two groups. Multivariate regression models will further adjust for residual confounding variables not fully balanced by PSM. Spearman and Pearson correlation analyses are used for the correlation analysis of normal distribution variables and non-normal distribution variables, respectively. Differences in diaphragmatic function parameters (DE, DTF) across multiple time points (T0–T3) will be analyzed using Linear Mixed-Effects Models (LMM) to account for within-subject correlation of repeated measures and robustly handle missing data. Differences in DEs at different times in the same subject were assessed by the Wilcoxon signed-rank test for matched data. Associations between postoperative DE reduction and clinically significant perioperative variables were analyzed using binary logistic regression analysis and reported as estimated crude advantage ratios and relative 95% CI. Similarly, binary logistic regression with stepwise variable selection (forward method) will be used to explore risk factors for PPCs, following the “Rule of Ten” (at least 10 events per candidate variable) to avoid model overfitting. To determine the predictive power of ultrasound parameters for PPCs, ROC curve analysis will be performed to validate the predefined PDD threshold (DE < 10 mm) rather than seeking a new cut-off, evaluating its discriminatory ability for PPCs. For the correlation analysis between diaphragmatic ultrasound parameters (DE, DTF) and ARISCAT scores, Pearson correlation analysis will be adopted if both variables conform to normal distribution, and Spearman correlation analysis will be used if the distribution is non-normal. On this basis, a combined predictive model for PPCs will be constructed by integrating ultrasound parameters (DE, DTF) and ARISCAT scores, and Net Reclassification Index (NRI) and Integrated Discrimination Improvement (IDI) will be used to quantify the improvement of the combined model in the discriminatory ability of PPCs prediction compared with the ARISCAT score single-factor model; the area under the ROC curve (AUC) of the single-factor model and the combined model will be further compared to verify the predictive efficacy of the integrated approach.

For missing data including unmeasurable left hemidiaphragm ultrasound measurements, Multiple Imputation (MI) will be used to handle incomplete observations at any time point (T0–T3), with 20 imputed datasets generated. Listwise deletion will not be adopted to avoid selection bias and preserve statistical power. All statistical analyses were performed using SPSS software Version 26.0 (IBM, United States) and R software (Version 4.3.0) with packages “lme4” (for LMM) and “mice” (for MI).

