**Methods:**

This is a single-center, prospective observational study conducted at the Affiliated Cancer Hospital of Guangzhou Medical University. A total of 148 patients scheduled for elective pulmonary resection (VATS or RATS) will be enrolled. Diaphragmatic function will be assessed using POCUS at four time points: 1 day preoperatively (T0), 30 min post-extubation (T1), and on postoperative day 1 (T2) and 3 (T3). The primary measurements include diaphragmatic excursion (DE) and diaphragmatic thickening fraction (DTF). The primary endpoint is the incidence of PDD (defined as DE < 10 mm or negative) on postoperative day 1. Secondary endpoints include the incidence and severity of PPCs within 7 days postoperatively (defined by European Perioperative Clinical Outcome criteria), serial changes in DE and DTF, pain scores, and quality of recovery (QoR-15). Propensity score matching and multivariate regression will be used to adjust for confounders.

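### The explicit confounder control serves VATS versus RATS; the primary PDD–PPC association is left to a stepwise model that need not yield an adjusted PDD odds ratio

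*Protocol article*

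**What the plan says.** The primary objective (2.6.1) is "To describe the incidence of postoperative diaphragmatic dysfunction (PDD) and explore its association with postoperative pulmonary complications (PPCs) after minimally invasive thoracic surgery". Surgical technique appears in the secondary objective (2.6.2), as a candidate risk factor for PPCs.

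The sizing (2.8) follows the primary objective: "Sample size is recalculated based on the primary predictive objective (logistic regression for the association between PDD and PPCs". Its inputs are "Assuming a PDD incidence of 30% postoperatively", a PPC incidence of 37%, and "an odds ratio (OR) of 3.0 for PDD predicting PPCs (7, 28), alpha = 0.05, power = 0.80", with 10% dropout. It names age, BMI and ASA class as covariates.

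In 2.9, propensity score matching is to balance baseline characteristics "between the VATS and RATS groups (1:1 matching ratio, caliper width 0.2 SD) to mitigate selection bias". The regression sentence follows: "Multivariate regression models will further adjust for residual confounding variables not fully balanced by PSM". The limitations at the end of the Discussion repeat that matching and covariate adjustment are there to balance VATS against RATS. The abstract drops that limit: "Propensity score matching and multivariate regression will be used to adjust for confounders".

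For PPCs, 2.9 specifies binary logistic regression with forward stepwise selection to explore risk factors, subject to ten events per candidate variable. A separate logistic analysis, of DE reduction, reports crude ratios. ROC and combined ARISCAT–ultrasound analyses follow. The article does not say whether the PPC analyses use the full or the matched cohort.

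**The concern.** The comparator in the primary objective and in the sizing is the patient without PDD. Matching VATS to RATS balances a different pair of groups. A variable such as COPD or pulmonary function (both recorded under 2.10) could be even across approaches, differ by PDD status and affect PPCs. Neither the matching nor the regression on its leftovers would deal with it.

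That leaves the stepwise model. Forward selection may leave PDD out, and then there is no adjusted odds ratio for the main exposure. If PDD enters, the variables beside it are those that passed an entry rule for PPC, not those needed to control confounding of PDD. At stake is whether the study's central association is reported with adjustment fixed in advance.

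**Working it through.** **1. Which tool serves which contrast**

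| Element | Contrast |
|---|---|
| Primary objective (2.6.1) | PPCs with versus without PDD |
| Sizing (2.8) | PPCs with versus without PDD, OR 3.0 |
| Matching (2.9) | VATS versus RATS |
| Regression on residual imbalance (2.9; limitations) | VATS versus RATS |
| Stepwise PPC model (2.9) | Any risk factor; PDD not forced in, no fixed confounders |
| Abstract | No contrast named |

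No row gives a pre-specified adjusted analysis of the primary contrast.

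**2. Reproducing the 148**

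Inputs from 2.8: PDD 30%, overall PPC 37%, OR 3.0, alpha 0.05 (taken as two-sided), power 0.80, dropout 10%.

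- Let P0 and P1 be the PPC risks without and with PDD. Then 0.7·P0 + 0.3·P1 = 0.37 and P1 = 3·P0/(1 + 2·P0). This gives 1.4·P0² + 0.86·P0 − 0.37 = 0, so P0 = 0.292 and P1 = 0.553.
- Wald variance factor: v = 1/[0.7·P0(1 − P0)] + 1/[0.3·P1(1 − P1)] = 6.914 + 13.483 = 20.40.
- N = (1.960 + 0.842)²·v/(ln 3)² = 7.849 × 20.40/1.207 = 132.6, so 133.
- 133/0.90 = 147.8, so 148. The plan's figure reproduces.

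**3. Power by number analysed**

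Wald power = Φ(ln 3·√(N/v) − 1.960). The score (pooled two-proportion) version is shown beside it.

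| N | Wald | Score |
|---|---|---|
| 133 (full evaluable cohort) | 80.1% | 81.4% |
| 106 | 70.7% | 72.2% |
| 80 | 58.5% | 60.0% |

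The last two rows apply only if the model were run in the matched set. Matched N = 2 × 133 × share in the smaller arm × match rate. The article gives neither share nor rate, so both are assumed:

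- 106 arises from equal arms with 80% matched (2 × 133 × 0.5 × 0.8), or from a 40:60 split with all matched (2 × 133 × 0.4).
- 80 arises from a 30:70 split with all matched (2 × 133 × 0.3).
- Equal arms with complete matching lose essentially nothing.

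**4. Room for adjustment**

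Expected PPC events are 133 × 0.37 = 49.2. At ten events per variable that is four terms. PDD, age, BMI, ASA and approach make five with ASA as one term, and six with ASA I–III as a three-level factor. With no dropout, 148 × 0.37 = 54.8 events allow five.

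**The case against.** The strongest reply is that 2.9 already limits matching to VATS and RATS, that the residual-imbalance sentence belongs to that comparison, and that PPCs have their own model. All of that stands. A reader might infer that covariates for the PDD–PPC association will be picked by imbalance between VATS and RATS. The text does not support this: the stepwise model selects variables by their relation to PPCs, and COPD, pulmonary function and one-lung ventilation time are all recorded and could enter it.

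A reader might also infer that matching costs the study its 80% power. That is not supported either. Nothing places the PPC models in the matched set, and sizing on 148 patients in total points to the whole cohort.

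Nor is 1:1 caliper matching an error. It is a standard choice for a non-randomised comparison of approaches.

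It can further be said that the primary endpoint (2.7.1) is PDD incidence, which needs no confounder control, that the objective is exploratory, and that a full analysis plan may list the confounders. The first two points lower the stakes. The third does not close the gap. The point concerns what the article does fix: a forward stepwise procedure as its only multivariable PPC risk-factor model, which does not match a sizing built on one named exposure, and an abstract that credits the study with a confounder adjustment aimed at another contrast. Naming age, BMI and ASA in 2.8 shows the intention, but 2.9 carries it into no model.

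**Conclusion.** The point holds as a gap between objective and analysis. The stated confounder control addresses VATS versus RATS, the abstract presents it as general, and the primary PDD–PPC association has no analysis that guarantees an adjusted odds ratio. The size of any residual confounding cannot be computed from the article.

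The 148 patients and 80% power hold in the full cohort. The figures of 71–72% and 59–60% are a conditional note. They require the PPC models to be run in the matched set, together with the assumed splits and match rates, and they do not measure a defect in the plan as written.

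**What to change.** - **Abstract and 2.9:** state that propensity score matching and the regression for its residual imbalance apply to the VATS–RATS comparison only. The matching can stay as planned.
- **2.9, primary association:** specify a logistic model for PPC in all evaluable patients, with PDD forced in and a short confounder set fixed in advance by relation to both PDD and PPCs. The age, BMI and ASA already named in 2.8, plus surgical approach, are natural candidates. Under the plan's own Rule of Ten, about four terms including PDD are affordable, so at least one of these would have to go. The stepwise model can remain as a secondary exploration of risk factors.
- **2.9, prediction:** state that the ROC and ARISCAT analyses also use the full cohort.

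This costs wording only, with no new data or patients. One consequence should be acknowledged: under the Wald formula 148 reproduces with no allowance for correlation between PDD and the covariates. If the covariates explained 10% of the variance of PDD (an assumption), the effective N would be 133 × 0.9 = 119.7, and power about 76% (Wald) to 77% (score).

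### The general correlation rule in section 2.9 is reversed (Spearman for normal, Pearson for non-normal variables) and contradicts the ARISCAT rule in the same section

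*Protocol article*

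**What the plan says.** Section 2.9 (Statistical analysis) of the protocol article contains two rules for choosing a correlation coefficient.

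- **General rule**, with no limit on scope: "Spearman and Pearson correlation analyses are used for the correlation analysis of normal distribution variables and non-normal distribution variables, respectively".
- **Specific rule**, introduced by "For the correlation analysis between diaphragmatic ultrasound parameters (DE, DTF) and ARISCAT scores". For normal data, "Pearson correlation analysis will be adopted if both variables conform to normal distribution"; otherwise, "Spearman correlation analysis will be used if the distribution is non-normal".

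Nothing elsewhere in the article corrects or explains the general rule. Apart from DE/DTF with ARISCAT, section 2.9 names no pair of variables to be correlated.

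**The concern.** The word *respectively* ties the first coefficient to the first kind of variable and the second to the second. The general rule therefore prescribes the rank coefficient where normality holds and the product-moment coefficient where it fails. Convention runs the other way: the usual inference for Pearson rests on approximate bivariate normality, and Spearman is the fallback when that is doubtful.

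Two things are at stake. First, a non-normal pair analysed literally by the general rule would get Pearson, which can lose power when the skew is heavy. Second, with opposite rules in one section, either coefficient could be reported for DE/DTF against ARISCAT and described as following the protocol. A prespecified plan should not leave that choice open until the results are known.

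**Working it through.** **Step 1: the two rules side by side.**

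| Distribution | General rule | DE/DTF–ARISCAT rule |
|---|---|---|
| Normal | Spearman | Pearson |
| Non-normal | Pearson | Spearman |

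The assignments are opposite in both rows. The general rule has no scope limit, so it also covers DE/DTF against ARISCAT, and there the two conflict directly. For any other correlation, only the general rule applies.

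**Step 2: what depends on the general rule.**

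- The primary endpoint is the incidence of postoperative diaphragmatic dysfunction (PDD) on day 1 (section 2.7.1). It is a proportion and uses no correlation coefficient.
- The sample size of 148 comes from a logistic regression of pulmonary complications (PPCs) on PDD (section 2.8).
- Section 2.9 gives logistic regression to the correlates of DE reduction and to PPC risk factors, mixed models to the repeated DE and DTF measurements, and ROC, NRI and IDI to prediction.

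None of these uses the rule. What remains is secondary or exploratory correlation.

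**Step 3: what the reversal could cost.** The article states no figure to reproduce, so the cost was simulated.

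Inputs:
- Patients: 148 × (1 − 0.10) = 133.2, taken as 133 (sample size and dropout rate from section 2.8).
- Underlying correlation: 0.25 (assumption).
- Test: two-sided, p < 0.05.
- Skewed variables: exp(s·x) applied to standard normal x. Skewness is about 1.75 at s = 0.5, about 3.7 at s = 0.8 and about 11 at s = 1.2. A milder case has skewness of about 1. The degree of skew is an assumption; the article gives no distribution for any variable.

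| Scenario | Pearson power | Spearman power | Cost of the general rule as written |
|---|---|---|---|
| Both normal | 0.83 | 0.80 | 0.83 − 0.80 = 0.03 |
| Both mildly skewed (about 1) | 0.80 | 0.79 | 0.79 − 0.80 = −0.01 |
| Both moderately skewed (about 1.75) | 0.73 | 0.78 | 0.78 − 0.73 = 0.05 |
| Both strongly skewed (about 3.7) | 0.60 | 0.80 | 0.80 − 0.60 = 0.20 |
| Both extremely skewed (about 11) | 0.37 | 0.78 | 0.78 − 0.37 = 0.41 |
| Discrete 0–10 score with a normal variable | 0.80 | 0.78 | 0.78 − 0.80 = −0.02 |

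If only one variable is skewed the loss is smaller: 0.78 against 0.78 at skewness of about 1.75, 0.70 against 0.79 at about 3.7, and 0.57 against 0.79 at about 11. With a few thousand simulated samples per scenario, the standard error near a power of 0.8 is about √(0.8 × 0.2 / 3000) = 0.007. Differences of 0.01 or 0.02 are therefore not meaningful.

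**The case against.** The strongest reply is that this is a slip of word order with little consequence. The authors state the conventional rule correctly and in full for the only correlation they specify, so they evidently know it, and an analyst would probably follow it throughout. That is fair and lowers the weight of the point. It does not remove the error: the general sentence is complete, grammatical and wrong, and nothing in the article tells the analyst which rule prevails.

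Two stronger readings are tempting, and the document does not support them.

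- **That pain (NRS), Ramsay and chest-drainage data will be analysed with the wrong coefficient.** Section 2.7.2 lists NRS and Ramsay scores as secondary endpoints. Section 2.4.3.1 says sedation is scored to explore its influence on diaphragmatic function or pulmonary outcomes, and section 2.10 mentions a possible link between drainage time and diaphragmatic function. None of these places assigns a correlation coefficient. Correlation is a natural candidate, but that is inference.
- **That the reversal would roughly halve power.** A fall from about 0.8 to below 0.4 appears only when both variables have skewness of about 11. With mild skew in both variables, or a discrete 0–10 score against a normal variable, Pearson loses nothing detectable.

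**Conclusion.** The point holds as an error of statement. The general rule is reversed, and the protocol's own later sentence shows it, so no outside source is needed. It is not an omission that a fuller analysis plan would fill.

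Its consequence is small. It touches secondary or exploratory correlations only and does not threaten the study's main results. Under the assumptions above (133 patients, underlying correlation 0.25), following the general rule literally costs about 0.03 of power on normal data, nothing detectable with mild skew, about 0.05 with moderate skew in both variables, and 0.2 to 0.4 only with strong to extreme skew in both. Both the correlation and the skew are assumed, so these figures give a range and do not predict the loss in this study. The firmer reason to correct the sentence is that DE/DTF against ARISCAT now has two opposite prespecified instructions.

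**What to change.** Either change is enough:

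- swap the two names in the general sentence, so that Pearson is used when both variables are approximately normal and Spearman otherwise; or
- delete the general sentence and extend the DE/DTF–ARISCAT rule to every correlation analysis.

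The second is slightly cleaner. It leaves a single rule, and because that rule requires both variables to be normal before Pearson is used, it also settles pairs in which only one variable is normal.

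The cost is one sentence, best corrected before the data are analysed. No data collection, study conduct, sample size or other analysis changes.
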